**Fig. 1 Fig1:**
[figure not shown]
SPIRIT trial schematic

**Table 1 Tab1:** Impact, process and economic evaluation research questions

Impact evaluation *(primary research question)*	What is the impact of a package of gender-sensitive group-based problem-solving interventions at community and community-facility levels to improve protection, prevention, diagnosis and treatment of childhood pneumonia and infectious diseases on mortality of children under-5 years old in Kiyawa LGA, Nigeria?
**Process evaluation**	Which attributes, mechanisms, effects (intended and unintended) and contextual factors enable or prevent gender-sensitive group-based problem-solving interventions at community and community-facility levels to improve protection, prevention, diagnosis and treatment of childhood pneumonia and infectious diseases in Kiyawa LGA?
	How do various stakeholders understand their role in the process of childhood pneumonia prevention in Jigawa, and how does this perception shift through participation in community-level interventions?
	How do social norms around gender, participation and decision-making in the home shape participation and engagement in community-level interventions to tackle childhood pneumonia?
	How do power and social dynamics and relationships in the wider community shape channels of communication between families and practitioners, and how does this impact on the ability to implement and efficacy of community-facility referral pathways?
	Was the intervention delivered (including fidelity, dose, reach, intensity, adaptation and duration) as intended?
**Economic evaluation**	What is the cost per disability-adjusted life-year (DALY) averted of a package of group-based problem-solving interventions at community and community-facility levels to improve protection, prevention, diagnosis and treatment of childhood pneumonia and infectious diseases in Jigawa State, Nigeria?
	Is it cost-effective considering opportunity costs of current and projected health spending (i.e. what is the estimated net benefit of the intervention package)?
	If the intervention package is cost-effective, is it affordable given the budget required for scale-up in Jigawa State, Nigeria?

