#### PLA groups with integrated PDQS

Groups of approximately 20–30 men and women in each community will be convened. Group meetings will be held separately for men and women to allow gender norms to be respected, and tailor meetings to different locations and times. Groups are open to all community members, and sharing of group messages will be encouraged; men and women with young children and those currently pregnant will be particularly encouraged to join.

The groups will work through a four-phase PLA cycle, following an initial introductory session. The phases include the analysis of the situation and prioritisation of child health issues in their communities (phase 1), planning actions to tackle these issues (phase 2), implementing the selected strategies (phase 3) and collective self-evaluation (phase 4) (Fig. 3). The PDQS process focussed specifically on healthcare service quality issues, with group members and healthcare workers joining together to mutually agree on quality indicators and joint actions. PDQS will be incorporated into all 4 phases of the PLA cycle, where healthcare workers will attend men’s and women’s groups. Each phase can involve multiple physical meetings, decided on by group members (see the “Ethical considerations” section for details on COVID-19 mitigations). The completion of one PLA cycle is anticipated to take 4–5 months, and groups will repeat the cycle multiple times over the 18-month intervention period.

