**Secondary outcomes**	
Suspected pneumonia mortality rate	The number of confirmed* deaths classified by InterVA-5 as primarily attributable to acute respiratory infections amongst children aged 7 days–59 months, per 1000 livebirths reported by women in the cohort, in the last 12 months [21]
Pneumonia point prevalence	The proportion of children clinically assessed on the day of the survey who meet 2014 WHO IMCI definition for pneumonia or severe pneumonia, including hypoxemia [22, 46]
Women’s wellbeing	The mean Short Warwick-Edinburgh Mental Wellbeing Scale score amongst women aged 16–49 years [23]
*Treat*	
Knowledge of pneumonia	The proportion of women aged 16–49 who can name both fast and difficulty breathing as signs of pneumonia
Care-seeking for childhood illnesses	The proportion of caregivers who self-reported visiting a formal healthcare provider (including primary, secondary, private or government facilities) within 48 h of illness recognition, amongst those who reported their child has been sick in the previous 2 weeks
*Protect*	
Exclusive breastfeeding	The proportion of children aged 0–6 months whose caregiver self-reports exclusively breastfeeding
Vitamin A	The proportion of children aged 18–59 months with 2 doses of vitamin A
*Prevent*	
Vaccine coverage	The proportion of children aged 18–59 months with complete vaccine coverage according to the Nigerian Childhood Vaccination programme [24]**
Handwashing with soap	The proportion of households who self-report access to soap and water in their home for handwashing
Household air pollution	The proportion of households who self-report cooking indoors with wood/charcoal or dried grass

*Deaths which are verified by a field supervisor during a verbal autopsy visit

**Includes 1 dose BCG, 4 doses oral polio vaccine, 2 doses rotavirus vaccine, 3 doses DPT-Penta, 3 doses PCV-10 and 2 doses measles

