### Randomisation

The 33 clusters will be randomised using a 1:1 ratio between intervention and control. Randomisation will be done publicly, with representatives from the LGA and all the wards, following community consent for the study and the randomisation process. The names of the health facility clusters will be written on pieces of paper, folded and placed in a container by study staff. A community representative will then pull the folded pieces of paper out of the container one by one, in front of community witnesses. The first 17 will be assigned to the intervention, and the final 16 will be assigned to control. Due to the nature of the intervention, communities will not be blinded to their status; however, we will not inform data collectors of the intervention status of villages or that they work across intervention and control clusters, and investigators will be blinded during primary analysis.

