### Data collection

Data collection will be done by 20 female clinical data collectors recruited from Jigawa, with two field supervisors. They will work in teams of 3–4, accompanied by a lay data collector to support community mapping. A sub-set of data collectors will be retained between surveys to conduct prospective vital event reporting. Data will be collected using a custom-built CommCare application on Android tablets. The forms will have in-built skip patterns and cleaning rules to minimise data entry errors. Data will be uploaded daily to a central secure server, and participant ID and data cleaning checks will be conducted continually during the data collection period. Data collectors will be trained using a hybrid approach, with a mix of practical sessions, at-home assignments and online webinars over a 2-week period. This will be followed by a field pilot in a neighbouring LGA and mock interviews with a group of women in the community who took part in questionnaire co-design discussions.

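### Handwashing access and household air pollution rest on self-report alone from unblinded households, so answers that differ by arm could bias these two secondary comparisons towards the intervention

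*Protocol article*

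**What the plan says.** Table 3 lists two household-level outcomes under Prevent, both defined by what the household says. Handwashing with soap is "The proportion of households who self-report access to soap and water in their home for handwashing". Household air pollution is "The proportion of households who self-report cooking indoors with wood/charcoal or dried grass".

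The Randomisation section describes a public draw and states: "Due to the nature of the intervention, communities will not be blinded to their status". The same sentence adds a safeguard on the interviewer's side: "we will not inform data collectors of the intervention status of villages or that they work across intervention and control clusters".

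Under PLA groups with integrated PDQS, intervention communities choose child-health priorities and act on them, in cycles of 4–5 months repeated over 18 months. Table 1 gives the purpose of the group-based package as "to improve protection, prevention, diagnosis and treatment of childhood pneumonia and infectious diseases". The Control section gives every cluster, control included, a weekly radio drama that covers prevention.

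On staffing, "Data collection will be done by 20 female clinical data collectors recruited from Jigawa". Under Baseline and endline surveys, they interview in each sampled compound and screen the children there. No section adds a direct observation of soap and water or of the cooking place and fuel, or any other check on these two answers. The Analysis section compares the prevent and protect indicators between arms.

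**The concern.** Both outcomes describe practices that have a socially approved answer. A respondent who knows that the community is in a child-health programme has more reason to give that answer than one who does not. If this happens more in the intervention arm, the between-arm difference mixes true change with a change in reporting, and the mixed-effects model cannot tell them apart. The bias works in opposite directions on the two scales (soap and water over-reported, indoor solid-fuel cooking under-reported), but in both cases it favours the intervention.

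These two outcomes differ from the other self-reported ones. Exclusive breastfeeding and care-seeking within 48 hours cannot be seen during a visit. Soap and water can be, and the cooking place and fuel partly can. Elsewhere the protocol does check: a field supervisor verifies deaths, and pneumonia is assessed clinically. What is at stake is how far two secondary outcomes can be believed, not the mortality result.

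**Working it through.** The document gives no prevalence, intra-cluster correlation (ICC) or reporting error for these outcomes, so there is no stated figure to reproduce. Its sample-size statement concerns mortality only. The formulas below are general. Every p, r and ICC put into them is an assumption.

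**Size of the bias.** Let p be the true prevalence, equal in both arms (no true effect).
- Handwashing: if a fraction c of households without soap and water claim to have them, reported access is p + (1 − p)c. The difference between arms is (1 − p) × r, where r is c in the intervention arm minus c in control.
- Indoor cooking: if a fraction d of households that cook indoors with these fuels deny it, reported prevalence is p(1 − d). The difference is −p × r, where r is now the difference in d.

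| Outcome | p | r = 0 | r = 5% | r = 10% | r = 20% |
|---|---|---|---|---|---|
| Handwashing | 40% | 0 | +3 points | +6 points | +12 points |
| Handwashing | 50% | 0 | +2.5 points | +5 points | +10 points |
| Indoor cooking | 60% | 0 | −3 points | −6 points | −12 points |
| Indoor cooking | 80% | 0 | −4 points | −8 points | −16 points |

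Only the excess over control enters. At p = 40%, over-claiming of 10% in control and 20% in intervention gives 0.40 + 0.60 × 0.10 = 46% against 0.40 + 0.60 × 0.20 = 52%, again 6 points. Here r is an average over all intervention households that could misreport, so limited reach of the groups makes it smaller.

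**Chance of a false positive.** Take one household per compound (assumed) and 127 compounds in each of 32 clusters after losses. That gives 127 × 32 = 4064 households, or 2032 per arm if the clusters split 16 and 16. With the protocol's coefficient of variation of 0.74, the design effect is 1 + ((1 + 0.74²) × 127 − 1) × ICC.
- ICC 0.01: design effect 2.96, effective size per arm 2032/2.96, about 688.
- ICC 0.05: design effect 10.78, effective size about 189.
- ICC 0.10: design effect 20.55, effective size about 99.

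Under a normal approximation, with no true effect and r = 10%:

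| Comparison | ICC 0.01 | ICC 0.05 | ICC 0.10 |
|---|---|---|---|
| Handwashing, 50% v 55% reported | 46% | 16% | 10% |
| Indoor cooking, 80% v 72% reported | 94% | 44% | 26% |

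For example, in the first cell the standard error is √((0.50 × 0.50 + 0.55 × 0.45)/688) = 0.0269. Then 0.05/0.0269 − 1.96 = −0.10, which gives 46%. At r = 0 every cell returns to the nominal 5%. The spread shows how much depends on inputs that the document does not give.

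**The case against.** The strongest reply is that pressure to give the approved answer exists in both arms. The radio dramas reach every cluster, an earlier participatory radio programme covered the whole area, and COVID-19 brought its own handwashing messages. Only the difference between arms biases the comparison. Data collectors are not told the arm, which limits prompting. Groups have about 20–30 people and are planned at one per 500 population, roughly 4–6% of residents (20/500 to 30/500), while the surveyed compounds are a random sample of all compounds. All of this stands and argues for a small r. It does not make r zero: the groups run in intervention clusters only, sharing of their messages is encouraged, and withholding the arm from the interviewer does nothing about a respondent who knows it.

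A reader might infer that desirable answers will rise in the intervention arm alone, or that the groups coach households on handwashing and cooking. The documents support neither. The radio reaches both arms, and groups set their own priorities within child health.

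It can also be said that the data offer some check. Endline asks about exposure to the intervention, and the process evaluation observes 30 households in three intervention and three control clusters. These help interpretation but do not validate the answers. Exposure is not randomised and may change both behaviour and reporting, and 30 households are few.

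Finally, observation has faults. Households can set soap out, and a single visit outside cooking time may miss a recurring practice. The second fault is real enough that observation should not replace self-report for air pollution.

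**Conclusion.** The point holds as a modest improvement to measurement. Two secondary outcomes are fixed as self-report by unblinded households with no check, and reporting that differs by arm would bias both towards the intervention. The safeguards in the plan reduce this without removing it. The baseline survey cannot correct it either, because the differential reporting would arise after exposure.

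The size is not known. The figure of 6 points rests entirely on the assumed p = 40% and r = 10%, and a zero differential is possible. It would be wrong to read the calculations as an estimate of the bias in this trial, or as evidence that these outcomes will come out falsely positive. They show only that a modest differential could matter at this sample size, above all if the ICC is low. The definitions are stated openly and contradict nothing else in the protocol.

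**What to change.** **Handwashing.** At endline, have the data collector record on the existing tablet form whether soap and water are seen at the place used for handwashing, before any soap is handed over as the token mentioned under Consent. Make this the outcome and keep the self-report item as supplementary. Observation by staff not told the arm then makes use of the masking already planned.

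**Household air pollution.** Keep self-report as the outcome. Add the observed cooking place and fuel as a supporting check, compare agreement with self-report by arm, and interpret the self-report result with caution if disagreement differs between arms.

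Record the change as a dated amendment before the endline survey. At the stated trial status (15 September 2021) only the baseline survey was complete, and endline was planned for July–September 2022.

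**Cost.** Visits become slightly longer, in a survey planned at about 70 compounds a day, with no extra staff or visits. There may be no observed baseline value. That costs little, because the Analysis section plans baseline-to-endline change only for pneumonia prevalence, knowledge and care-seeking. Staged soap and cooking missed at a single visit remain as limitations to report.

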### Randomisation

The 33 clusters will be randomised using a 1:1 ratio between intervention and control. Randomisation will be done publicly, with representatives from the LGA and all the wards, following community consent for the study and the randomisation process. The names of the health facility clusters will be written on pieces of paper, folded and placed in a container by study staff. A community representative will then pull the folded pieces of paper out of the container one by one, in front of community witnesses. The first 17 will be assigned to the intervention, and the final 16 will be assigned to control. Due to the nature of the intervention, communities will not be blinded to their status; however, we will not inform data collectors of the intervention status of villages or that they work across intervention and control clusters, and investigators will be blinded during primary analysis.

### Sampling

During the formative phase, we conducted a community mapping exercise to create a sampling frame, enumerating all villages and the total number of compounds. We will sample proportionately to cluster size, with a minimum of 50 compounds per cluster. Simple random sampling will be used to generate a list of compound numbers within each cluster. During the baseline survey, data collectors will use an Expanded Programme of Immunization approach [25] to number all the compounds in a village, following these steps: (1) locating the centre of the village with support from a community gate keeper, (2) spinning a pen and walking in the direction it points, (3) numbering the first compound encountered as 1 and (4) walking in a clockwise direction until all compounds are numbered. They will then recruit the compounds according to the generated random sample. The same compounds will be included in all subsequent surveys, and GPS coordinates will be taken to facilitate follow-ups. All eligible women, and children under-five years of age who are under their direct care, residing within sampled compounds will be recruited.

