**Methods:**

This is a cluster randomised controlled trial, with integrated process and economic evaluations, conducted from January 2021 to September 2022. The trial will be conducted in Kiyawa Local Government Area, Jigawa State, Nigeria, with an estimated population of 230,000. Clusters are defined as primary government health facility catchment areas (*n* = 33). The 33 clusters will be randomly allocated (1:1) in a public ceremony, and 32 clusters included in the impact evaluation.

The trial will evaluate a locally adapted ‘whole systems strengthening’ package of three evidence-based methods: community men’s and women’s groups, Partnership Defined Quality Scorecard and healthcare worker training, mentorship and provision of basic essential equipment and commodities. The primary outcome is mortality of children aged 7 days to 59 months. Mortality will be recorded prospectively using a cohort design, and secondary outcomes measured through baseline and endline cross-sectional surveys.

Assuming the following, we will have a minimum detectable effect size of 30%: (a) baseline mortality of 100 per 1000 livebirths, (b) 4480 compounds with 3 eligible children per compound, (c) 80% power, (d) 5% significance, (e) intra-cluster correlation of 0.007 and (f) coefficient of variance of cluster size of 0.74. Analysis will be by intention-to-treat, comparing intervention and control clusters, adjusting for compound and trial clustering.

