### Design

This is a pragmatic community-based cRCT, following a formative phase of intervention development, concept testing and community engagement. Impact against the primary outcome will be evaluated using an open prospective cohort, recording vital events (pregnancies, births and under-five child deaths) amongst a random sample of women on a rolling 4-monthly basis. Secondary outcomes will be recorded during cross-sectional surveys conducted at baseline (January–March 2021) and end line (July–September 2022) (Fig. 1). The same random sample of compounds, and all eligible women and children residing in these compounds, will be included in both surveys and prospective cohort.

Clusters are defined as the geographical catchment area of the 33 government primary care facilities. Clusters range in population size from approximately 1680 to 24,200 (median 5840). All villages in Kiyawa LGA will be included in the study (*n* = 425 enumerated villages); however, the Kiyawa PHC cluster will be excluded from the impact evaluation as this facility is in a peri-urban area and provides a level of inpatient care—unlike the other primary facilities. Villages are made up of compounds, which are defined as the group of structures (including ‘households’) where extended families live and have shared resources.

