### Sample size

The under-five mortality rate in Jigawa was reported as 192/1000 livebirths in 2017 [26], and deaths in the first week of life may reasonably account for 15% of the total under-five deaths. More recently, a participatory radio programme on child health and COVID-19 was delivered across the LGA (June–December 2020) and vaccine coverage has increased (unpublished data), which we assume to have reduced mortality. We therefore used a conservative baseline mortality of 100 deaths amongst children aged 7 days to 59 months per 1000 livebirths. With the following parameters, we will have a minimum detectable effect size of 30% [6]: (a) 380 children per cluster, (b) 80% power, (c) 5% significance, (d) intra-cluster correlation of 0.007 [27] and (e) coefficient of variance of cluster size of 0.74. We assume on average there are three children under-five per compound (i.e. 127 compounds per cluster), and therefore, we will sample 4480 compounds overall to allow for ~ 10% loss to follow-up. The sample size was calculated using Stata’s *-clustersampsi-* command [28]. We will review these assumptions following the baseline survey.

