## Trial status

Protocol version 2.3 (10 January 2021). As of the 15th September 2021, the baseline survey has been completed and prospective vital signs surveys started. PLA groups have been set up and are running, and some components of health system strengthening implemented. The protocol history is as follows: v1.0 (20 August 2019); v1.1 (23 August 2019) process evaluation incorporated; v1.2 (2 September 2019) minor language edits; v1.3 (3 September 2019) ethical approval added; v2.0 (4 June 2020) COVID-19 adaptation included; v2.1 (14 June 2020) COVID-19 qualitative data collection procedures; v2.2 (20 October 2020) prospective vital events reporting added following TSC recommendation; v2.3 (10 January 2021) sample size calculation updated to include cluster size variance.

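### Sampling compounds in proportion to cluster size carries catchment-size variation into the sample: the stated inputs then give about 75% power, not 80%, and a flatter allocation of the same 4480 compounds would give more

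*Protocol article*

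**What the plan says.** The Sampling section fixes the allocation: "We will sample proportionately to cluster size, with a minimum of 50 compounds per cluster". The Design section gives catchment populations from about 1680 to 24,200, with a median of 5840.

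The Sample size section assumes a "conservative baseline mortality of 100 deaths amongst children aged 7 days to 59 months per 1000 livebirths" and 380 children per cluster at 80% power and 5% significance, with an "intra-cluster correlation of 0.007 [27] and (e) coefficient of variance of cluster size of 0.74". From these it concludes that "we will have a minimum detectable effect size of 30" per cent. It assumes three children under five per compound (127 compounds per cluster) and arrives at 4480 compounds after allowing about 10% for loss. It adds that the assumptions will be reviewed after the baseline survey.

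The Trial status section describes version 2.3 as "sample size calculation updated to include cluster size variance". It also reports that the baseline survey is complete. The Abstract has "32 clusters included in the impact evaluation". The Analysis section plans a mixed-effects logistic regression with random effects for compound and trial cluster, and mentions no population weights.

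**The concern.** How many compounds to take from each cluster is the trial's own decision, because the mapping exercise already supplies a compound count for every village. Catchments differ in size whatever the trial does. The analysed samples differ in size mainly because the allocation follows the catchments.

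Within a cluster, extra children add less and less. With an intra-cluster correlation of 0.007 and 2.7 children per compound after loss (3 x 0.9), 50 compounds are worth about 70 independent children and 140 compounds about 104. Adding compounds to an already large sample therefore buys less than adding them to a small one.

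Two things are at stake: whether the stated 80% and 30% follow from the stated inputs, and whether the same number of compounds could have bought more power. The Discussion itself names the power calculation as the main design challenge and admits a risk of being under-powered.

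**Working it through.** **Inputs.** From the Sample size section: control risk 0.10, a 30% reduction (so 0.07), mean m = 380 children per cluster, ICC = 0.007, CV = 0.74, 5% significance (two-sided assumed, as the article does not say). From the Abstract: 32 clusters. I take 16 per arm. This is an assumption, because the Randomisation section says "The first 17 will be assigned to the intervention, and the final 16 will be assigned to control" and the arm of the excluded cluster is not fixed.

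**Compound count.** 32 x 140 = 4480, and 127 x 32 x 1.1 = 4470, so the total of 4480 reproduces.

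**Stated power, standard formula.**
- Design effect = 1 + ((1 + CV²)m - 1) x ICC = 1 + (1.5476 x 380 - 1) x 0.007 = 5.11.
- Effective children per arm = 16 x 380 / 5.11 = 1190. Individual randomisation would need 1356 per arm for 80% power.
- Power = Φ[(0.03√1190 - 1.96√(2 x 0.085 x 0.915)) / √(0.10 x 0.90 + 0.07 x 0.93)] = Φ(0.66) = 74.7%.
- Detectable reduction at 80% power: 31.9%.
- Clusters needed per arm: 1356 x 5.11 / 380 = 18.2, against 16 available.

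The stated 80% and 30% are not reproduced. Other versions of the calculation also miss:

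| Variant at CV 0.74 | Power |
|---|---|
| Unpooled variance | 74.8% |
| t distribution, 30 df | 71.9% |
| 16.5 clusters per arm | 76.0% |
| m = 420 | 75.5% |
| One-sided 5% | 83.7% |

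**Effect of the floor.** The individual cluster sizes are not given, so I simulated 32 sizes with CV 0.74 (lognormal and gamma) and applied the floor of 50 compounds. The realised CV is about 0.67. The design effect is then 1 + (1.4489 x 380 - 1) x 0.007 = 4.85, effective n is 6080 / 4.85 = 1254 and power is about 77%.

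**Equal allocation, same total, same formula.** With CV = 0 the design effect is 1 + 379 x 0.007 = 3.65. Effective n is 6080 / 3.65 = 1664 per arm, power is 87.4% and the detectable reduction is 27.3%. Clusters needed per arm: 13.0.

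**Under the planned mixed model.** A cluster of m children contributes about m / (1 + (m - 1) x ICC), so large clusters are already down-weighted.
- Approximation without the floor: L = 380 x 0.007 / (0.993 + 2.66) = 0.728. Relative efficiency = 1 - 0.5476 x 0.728 x 0.272 = 0.892. Effective n = 1664 x 0.892 = 1484, power 83.4%.
- Simulated lognormal sizes with the floor: effective n about 1543, power 84.9%.
- Equal allocation: effective n about 1662, power 87.4%. The gain over 1543 is 1662 / 1543 = 1.08, or about 8% more information.
- An equal sample matching 1543 needs about 295 children per cluster. That is 295 / 2.7 = 109 compounds, and 109 x 32 = 3488, or about 3,500 instead of 4480.

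**Sensitivity (standard formula, proportional v equal).** Control risk 8%: 64% v 79%. ICC 0.003: 95% v 98%. ICC 0.015: 47% v 63%. The ordering does not change.

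**Feasibility.** With 25% of the population under five and three such children per compound, there are about 12 people per compound. The smallest catchment then has 1680 / 12 = 140 compounds. A sample of 140 is a full census there, with no slack.

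**The case against.** The strongest objection is that the larger gain belongs to a formula and not to the planned analysis. The 1 + CV² design effect makes no allowance for a mixed model's down-weighting of large clusters. With that allowance, proportional sampling already exceeds 80% at the protocol's inputs, and flatter allocation adds only about 2.5 to 4 points. This stands and sets the size of the point. It does not rescue the stated calculation, which includes the CV and does not reproduce on the standard formula.

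Second, proportional sampling is roughly self-weighting for children in the local government area (LGA). If an equal sample were reweighted to population, effective n would fall to 1664 / 1.5476 = 1075 and power to about 70% (assuming a population CV of 0.74). This is a real cost for area-wide descriptive estimates. It does not decide the primary comparison: the Analysis section specifies no population weights, and under proportional sampling the mixed model already weights clusters nearly equally (CV of the cluster weights about 0.17).

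Three stronger readings are tempting, and the documents do not support them.
- That the sampling rule creates the 0.74. The article does not say whether 0.74 describes catchments or samples, and the floor lowers the realised value.
- That the 24,200-person catchment shows how much fieldwork is wasted. The stated range covers all 33 clusters, and the largest may be the peri-urban one excluded from the impact evaluation.
- That the change costs nothing in the field. The number of compounds is unchanged, but travel costs by cluster are not given.

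**Conclusion.** The point holds in two parts. First, the stated 80% power for a 30% reduction does not follow from the stated inputs on the standard size-variation formula, which gives about 75% and 32%, or about 77% power once the floor of 50 is allowed for. Second, equal or near-equal allocation of the same 4480 compounds is more efficient for the primary comparison: about 87% and 27% on that formula, but only about 83-85% rising to 87% under the planned mixed model.

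A reader might infer that the trial is bound to fall short of 80%. That does not follow, because at the protocol's inputs the mixed model puts proportional sampling above 80%.

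The figures assume 16 clusters per arm, a two-sided test, and 100 per 1000 as the 12-month risk per child, as the protocol does. Like the protocol's own calculation, they use a single intra-cluster correlation and no separate compound-level one. The mixed-model figures also depend on the assumed shape of the size distribution.

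**What to change.** In the Sampling section, replace proportional allocation with an equal or near-equal number of compounds per evaluated cluster (about 140 x 32 = 4480), capped at the compounds available, with any shortfall reallocated to other clusters. In the Sample size section, use the CV of the sampled and not the catchment sizes, name the formula or model behind it, and restate the power and detectable effect. Use the known sampling fractions as weights for LGA-wide descriptive estimates.

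The baseline survey is complete and the same compounds are followed throughout, so changing the allocation now would mean re-drawing a recruited cohort. If that cohort is kept, make the restatement alone, using the realised sample sizes. The review of assumptions promised after baseline is the natural place for it, and it costs only a recalculation.

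A changed allocation would bring a near-census of the smallest catchments, travel costs by cluster that the article does not give, and a sample no longer self-weighting for the area.
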